## **3 Study design**

### **3.1 Description of the study**

Phase 1 study of NCC LungReal study is a retrospective, multicenter, electronic health record

(EHR)-based, real-world study. Figure 1 illustrates the study design.

Phase 1 study of NCC LungReal study enrolls patients who underwent surgical resection for lung cancer during the time period from January 2014 to December 2021.

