## **3.3 Patient enrollment**

### ***3.3.1 Inclusion criteria***

Patients who were admitted to the enrolled participating medical centers between January 2014 to December 2021 and met any of the following criteria are eligible for study entry:

- (1) Diagnosis of lung cancer and presence of lung surgery record.

- (2) Diagnosis of lung cancer and presence of pathology report containing  $\geq 60$  Chinese characters.
- (3) Diagnosis of lung cancer and presence of lung surgery in the data field of “operation” in the front page of EHR.
- (4) Diagnosis of lung cancer and admitting department is (thoracic) surgery department.

“Diagnosis of lung cancer” requires any one of the following:

- Diagnoses on the front page of EHR include typical Chinese terminology for “lung cancer” and/or “lung malignancy” defined by the Study Committee.
- ICD-9 code on the front page of the medical record includes “162.”
- ICD-10 code on the front page of the medical record includes “c34.” or “c39.9”.
- ICD-O-3 code on the front page of the medical record includes any of xxxx/3 code in the list of 2015 WHO classification of lung tumors.
- Name of the surgery included typical Chinese terminology for lung cancer surgery, determined by the Study Committee.
- Pathology diagnosis includes terminologies for “lung cancer” and/or “lung malignancy” defined by the Study Committee.

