### ***3.3.2 Exclusion criteria***

Patients who meet any of the following criteria will be excluded from study entry:

- (1) Lacking raw data from the front page of the EHR.
- (2) Lacking a pathology report of the surgically resected specimen.
- (3) Lacking information required to link raw data from different sources together.

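### The written eligibility rules do not require a lung resection, so some lung cancer patients whose only resected specimen is not lung can enter a cohort defined by resection for lung cancer

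*Protocol*

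**What the plan says.** Protocol section 3.1 says that the study "enrolls patients who underwent surgical resection for lung cancer during the time period" January 2014 to December 2021. Section 2.1 sets a target of at least 60,000 patients, described in the same terms.

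Section 3.3.1 makes patients eligible if they "met any of the following criteria are eligible for study entry". The four routes are:

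- Route (1): "Diagnosis of lung cancer and presence of lung surgery record".
- Route (2): "Diagnosis of lung cancer and presence of pathology report containing" at least 60 Chinese characters.
- Route (3): "Diagnosis of lung cancer and presence of lung surgery in the data field of" operation on the front page of the health record.
- Route (4): "Diagnosis of lung cancer and admitting department is (thoracic) surgery department".

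Any one of six signals establishes the diagnosis. The first is "Diagnoses on the front page of EHR include typical Chinese terminology for" lung cancer or lung malignancy. It need not be the principal diagnosis or the reason for the operation.

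Section 3.3.2 excludes patients with no front page, patients whose data cannot be linked, and, under (2), those "Lacking a pathology report of the surgically resected specimen".

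**The concern.** Routes (1) and (3) name lung surgery; routes (2) and (4) do not. Because the routes are alternatives, the loosest ones set the entry rule. Of the three exclusions, only 3.3.2(2) concerns what was removed, and it names neither the organ nor the lesion. The written rule is therefore wider than the population in sections 2.1 and 3.1.

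Overall survival is the primary outcome (section 3.4), and section 2.5 plans to report it overall and by stage, treatment pattern and period. Patients without a lung resection may have a different prognosis. Where they are patients with advanced disease, they would fall in the small advanced-stage strata. Their share could also vary by centre and year with the way departments and pathology text are recorded, which would affect the planned temporal trends.

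**Working it through.** **Eligibility logic.** The protocol gives no figure to reproduce here, so the check is of the rule itself. As written, a patient is eligible if: diagnosis AND [route (1) OR (2) OR (3) OR (4)] AND NOT [exclusion (1) OR (2) OR (3)]. In the table every patient has a lung cancer diagnosis, a front page and linked data.

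| Patient | Route met | Exclusion (2) | As written | With a lung-resection condition |
|---|---|---|---|---|
| Lobectomy | all four | not triggered | eligible | eligible |
| Needle or bronchoscopic biopsy only | (2), perhaps (4) | triggered | not eligible | not eligible |
| Resection of another organ only | (2) | not triggered, read literally | eligible | not eligible |
| Surgical node or pleural excision only, tissue counted as resected | (2), perhaps (4) | not triggered | eligible | not eligible |
| The same, tissue not counted as resected | (2), perhaps (4) | triggered | not eligible | not eligible |
| Lung cancer metastasis resected, no lung operation | (2) | not triggered | eligible | not eligible, unless the protocol chooses to include it |

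**Other safeguards.** Section 4.4.4 has surgery names curated by two surgeons, but no section makes them an entry condition. Section 4.3.1 has data managers check pathology text for a surgical-specimen report and a lung cancer diagnosis; the organ resected is not on the list. That check covers 12,000 sampled cases, at most 12,000/60,000 = 20% of the minimum cohort. It is defined as a measure of accuracy, and no rule for removing patients is attached to it.

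**Size, whole cohort.** All inputs are assumptions: 5-year survival of 75% in true resections and 15-30% in the others, and a contaminated share c of 1-3%. The shift is c × (survival in the others − 75%).

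- c = 1%, 30%: 0.01 × (30 − 75) = −0.45 points.
- c = 1%, 15%: 0.01 × (15 − 75) = −0.60 points.
- c = 3%, 30%: 0.03 × (30 − 75) = −1.35 points.
- c = 3%, 15%: 0.03 × (15 − 75) = −1.80 points.

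On a cohort of 60,000, 1-3% is 600 to 1,800 patients.

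**Size, one small stratum.** Again all assumed: 1,200 true stage IV resections (2% of 60,000) with 40% survival, joined by other patients with 15% survival.

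- 300 join: (1,200 × 0.40 + 300 × 0.15)/1,500 = 525/1,500 = 35.0%; share 300/1,500 = 20%.
- 600 join: (1,200 × 0.40 + 600 × 0.15)/1,800 = 570/1,800 = 31.7%; share 600/1,800 = 33%.

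At c = 1% (600 patients), the second line needs every one of them to be stage IV; the first needs half.

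**The case against.** The strongest reply is that exclusion (2) should be read with sections 2.1 and 3.1. Its definite article most naturally points to the resection for lung cancer named there. On that reading the design is a wide search, which recovers patients with a missing operation field, followed by a resected-specimen filter. This is probably the intent. It does not settle the matter, because the rule must be applied to health-record data from at least 12 centres with no limit on type (section 3.2.1), and the organ has to be stated for that.

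Other parts of the reply stand:

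- A reader might infer that biopsy-only patients enter freely. They do not: exclusion (2) removes needle and bronchoscopic biopsies. Only surgical excisions whose tissue is read as a resected specimen remain open.
- A reader might infer that a resected metastasis is plainly ineligible. Section 3.1 speaks of resection for lung cancer rather than of the lung, so such a patient arguably fits. This is a question of scope that the protocol leaves open.
- The manual check would probably flag a report showing only a non-lung tumour, since it would not confirm lung cancer. It would do so only within the sample.
- Curated surgery names and processed gross descriptions (section 4.4.2) make non-lung operations identifiable, and an analysis plan could remove them. Eligibility is nevertheless fixed in section 3.3, and that is where the rule is too wide.
- The size of the 60,000 target is not at stake. It is a database goal, not a power calculation.

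**Conclusion.** The point holds on the text. The entry rule in section 3.3 admits patients outside the population of sections 2.1 and 3.1. The clearest case is a lung cancer patient whose only resected specimen is from another organ. A surgical node or pleural excision is a conditional case, and a resected metastasis is a scope choice to be stated.

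The documents do not show how many such patients there are; the number could be negligible. Under the assumed 1-3% share and 15-30% against 75% survival, the whole-cohort effect is modest, about −0.45 to −1.8 points. A small stratum could move further, in the illustration from 40% to between 35.0% and 31.7%. That range depends wholly on assumed figures, above all on how many of the extra patients are stage IV. Node excision does not by itself imply stage IV, and a patient with another resected tumour may have lung cancer of any stage. It would therefore be wrong to conclude that the protocol's stage IV survival will be understated by a known amount, or that the cohort is known to be contaminated.

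**What to change.** Keep routes (1) to (4) as search routes. Add to section 3.3.1 one condition for every patient: evidence that lung tissue was resected, found in the surgery record, the front-page operation field or the specimen description of the pathology report. Reword exclusion (2) in section 3.3.2 so that the required report is of the resected lung specimen. State whether patients whose only operation removed a lung cancer metastasis belong to the cohort.

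Accepting any of the three sources matters. Relying on the surgery record or operation field alone would drop genuine resections with missing operation data.

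The cost is a few sentences in section 3.3, a written amendment with ethics approval (section 6.4), and one filter on surgery and pathology data that section 2.3.1 already gives high priority. The cohort becomes slightly smaller, and a few true resections with poor operation and specimen text may be lost.

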#### ***4.3.1 Accuracy of patient enrollment***

The accuracy of patient enrollment is defined as the proportion of patients enrolled that were confirmed by a human check.

As the lack of sex, age, and poor quality of internal linkage can be easily checked automatically, human resources are prioritized towards checking the presence of pathology reports for surgical specimens and the diagnosis of lung cancer. Trained data managers will check the raw text of the pathology report of enrolled patients to determine the presence of pathology reports for surgical specimens and the diagnosis of lung cancer. A total of 12,000 cases will be stratified-sampled from the included medical centers for accurate enrollment.

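### The eligibility rules in 3.3 never require the resected specimen to show primary lung cancer, so patients with another primary, a metastasis from elsewhere or benign disease can enter the cohort

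*Protocol*

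**What the plan says.** Entry under Protocol 3.3.1 needs a lung cancer diagnosis plus one of four conditions.

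The diagnosis "requires any one of the following", and six routes follow. Three of them matter here:
- an ICD-O-3 entry on the front page that "includes any of xxxx/3 code in the list of 2015 WHO classification of lung tumors";
- a front-page term ("Diagnoses on the front page of EHR include typical Chinese terminology for" lung cancer or lung malignancy);
- an operation name ("Name of the surgery included typical Chinese terminology for lung cancer surgery, determined by the Study Committee").

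Of the four conditions, (1) and (3) call for a record of lung surgery. The other two do not:
- (2) reads "Diagnosis of lung cancer and presence of pathology report containing" at least 60 characters, with no organ or result specified;
- (4) reads "Diagnosis of lung cancer and admitting department is (thoracic) surgery department".

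Section 3.3.2 has three exclusions: no front-page data, no linkage information, and "Lacking a pathology report of the surgically resected specimen". None concerns the content of the report.

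Section 4.3.1 plans a manual reading of pathology text in 12,000 sampled patients: "The accuracy of patient enrollment is defined as the proportion of patients enrolled that were confirmed by a human check".

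**The concern.** Sections 2.1 and 3.1 describe the population as patients resected for lung cancer. The rules in 3.3 do not guarantee it. The ICD-9 and ICD-10 routes are site codes. The ICD-O-3 route is written as a morphology and behaviour code, and no topography code has to accompany it. The front-page and operation-name routes need no support from pathology. Once a patient is in by any route, a report showing something other than primary lung cancer does not take the patient out.

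Overall survival is the primary outcome (3.4). Section 2.5 uses it for the whole population and for strata including histology and period of surgery, along with time trends and prognostic factors. Wrong inclusions would affect all of these. They could also vary by centre and year, because 3.2.1 sets no limit on the type or level of centre and coding habits may differ. The documents give no data on that variation.

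**Working it through.** **1. Logical check.** Entry = (any of six diagnosis routes) and (any of four conditions) and (none of three exclusions). Two test cases:

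| | Case A: non-lung carcinoma resected in a thoracic surgery department | Case B: front-page lung cancer term or lung cancer operation name; specimen benign or metastatic from elsewhere |
|---|---|---|
| Diagnosis route | ICD-O-3 /3 code, if its morphology is also on the lung list | front-page term or operation name |
| Condition | (2) or (4) | any of (1) to (4) that applies |
| Front page and linkage present | yes | yes |
| Report of resected specimen exists | yes | yes |
| Result under 3.3 | enters | enters |

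Case A depends on a histologic type being shared between organs. The documents do not reproduce the code list; they show only that no site code is required. Case B does not depend on the code list, so the gap exists without Case A.

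**2. Reach of the 4.3.1 check.** Inputs: minimum cohort N = 60,000 (2.1); sample n = 12,000 (4.3.1).
- Checked share at the minimum cohort size: 12,000 / 60,000 = 20%. Unchecked: 60,000 − 12,000 = 48,000 (80%).

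The documents give no false-inclusion rate, so e is assumed. Wrong inclusions = N × e. Those left even if every one found in the sample were removed = (N − n) × e. Half-width of the 95% interval = 1.96 × √(e(1 − e)/n), treating the stratified sample as simple random.

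| Assumed e | Wrong inclusions in 60,000 | Left in the unchecked 48,000 | Half-width (percentage points) |
|---|---|---|---|
| 1% | 600 | 480 | 0.18 |
| 2% | 1,200 | 960 | 0.25 |
| 5% | 3,000 | 2,400 | 0.39 |

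The check would measure the error well. It does not remove it.

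**3. Effect on 5-year overall survival.** Shift = e × (S_other − S_lung). The survival gap is also assumed: 20 to 30 points, all in one direction (higher for benign disease, lower for other cancers).
- e = 1%: 0.01 × 20 = 0.2 points; 0.01 × 30 = 0.3 points.
- e = 5%: 0.05 × 20 = 1.0 point; 0.05 × 30 = 1.5 points.

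If both kinds of error occur, the terms have opposite signs and partly cancel in the whole cohort. Within a histology stratum, e is the fraction in that stratum. It may be larger than in the whole cohort, and benign cases, having no malignant histology, would not offset other cancers there.

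**The case against.** The strongest reply is that broad screening of routine records, with accuracy and coverage both measured, is a coherent design. Section 4.3.1 has trained staff read pathology text for exactly this error in a large sample, and 4.3.2 compares enrolment with an external list of 8,000. Section 3.3 governs entry to a database. Section 2.5 limits analyses to data it calls qualified, and a restriction to confirmed cases could be set out in a statistical analysis plan that is not shown.

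Part of this stands. A reader might infer that the survival results are contaminated; the documents do not show that. They give no false-inclusion rate, no survival gap and no count of patients admitted by the morphology code alone, so the supportable word is *can*. A reader might also take the front-page term or operation name to be a pre-operative label; the protocol does not say when either was recorded. Nor does a single item suffice for entry: one of the four conditions must hold too, and requiring a report of a resected specimen removes unoperated patients. A shift of 1.5 points is the top of an assumed range with all error in one direction.

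What does not stand is that the safeguards close the gap. Section 4.3.1 sets no acceptance threshold and no rule for unconfirmed patients. Section 4.3.2 looks for eligible patients who were missed, which is the opposite error. The data quality evaluation in 4.5 asks whether values were extracted faithfully, and a correctly extracted benign report would pass. The protocol does not define what makes data qualified. Eligibility is fixed in the protocol, and as written it is wider than the stated population.

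**Conclusion.** The point holds as a fault in the stated eligibility rule, of unknown size. Sections 3.3.1 and 3.3.2 together can admit patients whose resected specimen shows a non-lung primary, a metastasis from elsewhere or only benign disease, and 4.3.1 measures this without correcting it. The logical gap rests on the text alone.

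The range of 0.2 to 1.5 points in whole-cohort 5-year survival rests on two assumptions outside the documents: 1% to 5% false inclusion and a 20 to 30 point gap in one direction. A mixture of errors would bring it lower; a histology stratum could see more. It is worth correcting because the remedy is small and uses a report already required for every patient, not because serious bias has been demonstrated.

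**What to change.** 1. In 3.3.1, count the ICD-O-3 morphology code only together with a lung topography code or a lung-specific diagnosis term.
2. In 3.3.2, or in the definition of the analysis set, exclude patients whose processed resection pathology shows only benign disease, a metastasis to the lung from a non-lung primary, or a non-lung primary. State explicitly that lung primaries with metastasis stay in, as do patients with previously proven lung cancer and no residual tumour in the specimen. A bare exclusion of metastatic pathology would wrongly drop the former.
3. In 4.3.1, state that patients not confirmed by the manual check are removed.

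Cost: a few lines of text and a filter on processed pathology, which 2.3.1 already ranks as high priority. Section 4.4.2 does not list a benign, metastatic or other-primary element by name, so one may have to be derived. The filter can run only after the pathology modules have processed the reports (development from December 2021, per 4.7), which is a reason to consider placing it in the analysis set. Expect slightly fewer patients, some borderline cases to adjudicate, and some wrongful exclusions from extraction errors. The evaluation in 4.5.2, planned for at least 12,000 cases, can estimate how often the last occurs.

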### ***3.3.2 Exclusion criteria***

Patients who meet any of the following criteria will be excluded from study entry:

- (1) Lacking raw data from the front page of the EHR.
- (2) Lacking a pathology report of the surgically resected specimen.
- (3) Lacking information required to link raw data from different sources together.

### **3.4 Outcome measurement**

Overall survival (OS) is the primary outcome measurement.

OS is defined as the time from surgery to death from any cause. Patients who are lost to follow-up, or alive at last contact will be censored at last contact.

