#### **4.6 Follow-up and outcome**

Follow-up and outcome data for included patients will be collected from multiple sources and harmonized by the Study Committee.

- Patients' visits or re-admissions to participating centers will be exported from NCID.
- Results of routine follow-up contacts through telephone calls performed by participating medical centers.
- National Cancer Center and Chinese Center for Disease Control and Prevention have established a cooperation framework, namely National Cancer Data Linkage (NCDL) Platform of

China [China CDC Wkly.2022;4(13):271-275.]. Death events collected by China CDC will be linked to NCC through NCDL and harmonized.

- The Study Committee plans to perform active follow-up. Due to the large number of enrolled patients, a relatively long interval (every 3 to 4 years) between each round of active follow-up is expected.

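### The last-contact censoring rule for OS does not fit a follow-up system that adds deaths-only registry linkage; if deaths linked after last contact are counted, 5-year OS is probably biased, usually downward

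*Protocol*

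**What the plan says.** Protocol section 3.4 names OS as the primary outcome. The event is broad: "OS is defined as the time from surgery to death from any cause". The censoring rule follows: "Patients who are lost to follow-up, or alive at last contact will be censored at last contact". Last contact is not defined, and no common cut-off date is given.

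Section 4.6 lists four sources. Three can show that a patient is alive, and each needs contact with the patient:

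- Hospital attendance: "Patients' visits or re-admissions to participating centers will be exported from NCID".
- Centre calls: "Results of routine follow-up contacts through telephone calls performed by participating medical centers".
- Active rounds planned by the Study Committee, for which "a relatively long interval (every 3 to 4 years) between each round of active follow-up is expected".

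The fourth supplies deaths only: "Death events collected by China CDC will be linked to NCC through NCDL and harmonized".

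On combining the sources, the section says only: "Follow-up and outcome data for included patients will be collected from multiple sources and harmonized by the Study Committee". The protocol gives no linkage end date, no linkage coverage, and no rule for a death linked after last contact. Section 2.5 uses OS for the whole cohort, for subgroups (including period of surgery) and for prognostic factors.

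**The concern.** Take two patients last seen in 2016. One dies in 2020 and the death is found by linkage. The other is alive in 2022 but has had no further contact. If the linked death counts, the first patient stays at risk until 2020 and contributes an event. The second leaves the risk set in 2016. After last contact, the risk set keeps patients who will die and drops those who will not. Kaplan-Meier and Cox methods assume that this does not happen.

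The primary outcome is at stake. Section 2.1 plans at least 60,000 patients, so sampling error is small: at 40% survival and before allowing for censoring, the standard error is √(0.4 × 0.6 / 60,000) = 0.2 points. A bias of even 1 or 2 points would dominate it. If loss of contact differs between centres, periods or patient groups, comparisons between them would be distorted too.

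**Working it through.** The protocol states no survival estimate or calculation on this point, so there is no figure of its own to reproduce. Three rules are compared:

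- **A**: linked deaths count at any date; survivors are censored at last contact.
- **B**: everyone is censored at last contact; later linked deaths are ignored.
- **C**: linked deaths count; survivors are censored at a common linkage date.

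**Hand example (all figures assumed).** Of 100 patients followed for 5 years, 20 die and 80 survive. Twenty, chosen at random, lose contact directly after surgery; 4 of them die and 16 survive.

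- A: the 16 lost survivors drop out at time 0, leaving 84 at risk with 20 deaths. OS = 64/84 = 76.2%.
- B: all 20 lost patients drop out, leaving 80 at risk with 16 deaths. OS = 64/80 = 80%.
- C: 100 at risk with 20 deaths. OS = 80%.

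If only 2 of the 4 later deaths are linked, A gives 64/82 = 78.0% and C gives 82/100 = 82%. So A errs downward, and C errs upward once linkage is incomplete.

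**Simulation with loss spread over time.** From the protocol: 60,000 patients (2.1), surgery from January 2014 to December 2021 (2.1), and data collection closing on 31 August 2022 (4.7), used as the end of observation. The low survival anchor of about 40% at 5 years is the background figure in section 1. Assumed: 80% as a second survival level, exponential survival, uniform entry, loss of contact by 5 years of 10% to 50%, and linkage completeness. Monte Carlo error is about 0.2 to 0.4 points.

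Rule A, non-informative loss, complete linkage, 5-year OS:

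| Loss by 5 years | True 40% | Fall | True 80% | Fall |
|---|---|---|---|---|
| 10% | 38.7% | 1.3 | 79.1% | 0.9 |
| 20% | 37.1% | 2.9 | 78.7% | 1.3 |
| 30% | 35.8% | 4.2 | 77.0% | 3.0 |
| 50% | 31.9% | 8.1 | 74.0% | 6.0 |

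The 1.3 at 20% loss and true 80% comes from a sample that ran high. Rule B gave 80.6% in the same run, so the fall against it is 80.6 − 78.7 = 1.9. Otherwise B and C return about the true value. At 50% linkage the fall under A is roughly half; with no loss or no linkage it is zero.

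**Informative loss.** Now suppose that 40% of patients lose contact 0 to 6 months before death, with 20% other loss. Rule A gives:

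| Linkage | True 40% | True 80% |
|---|---|---|
| 50% | 46.0% | 82.8% |
| 70% | 42.1% | 80.8% |
| 90% | 38.7% | 78.8% |
| 100% | 36.8% | 78.1% |

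The sign changes between 70% and 90% linkage. Rule B fails badly here, at about 57% against 40% and 87.5% against 80%.

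**Re-contact.** In a second loss model (true 80%, complete linkage), 20%, 40% or 60% of patients lose contact within 3 years. If the loss is permanent, rule A gives 77.4%, 73.8% and 68.2%. If one active round at data close reaches 70% of lost survivors (assumed), it gives 79.3%, 78.5% and 77.5%. Two groups with the same true OS but 20% and 60% loss would appear 77.4 − 68.2 = 9.2 points apart without re-contact, and 79.3 − 77.5 = 1.8 points apart with it.

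**The case against.** The strongest reply is that the protocol nowhere says a death linked after last contact counts. Read literally, section 3.4 censors a patient lost to follow-up at last contact, with no exception for a later linked death. That is rule B, which is unbiased if loss is non-informative. Nor does the text exclude treating a negative linkage check as a contact. An SAP, not shown here, might settle precedence and cut-off dates.

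This stands in part: counting later deaths is an inference, though the natural one. Rule B would discard the very deaths that linkage adds for patients out of contact, and it sits badly with an any-cause definition. The two readings give different OS. Because the protocol itself fixes both the censoring rule and the sources, an SAP that followed section 3.4 would inherit the mismatch.

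A reader might also infer that OS in the whole cohort and in every subgroup is certain to be biased downward. The documents do not support that. Sign and size depend on loss, linkage coverage and the reason contact stops, and the protocol reports none of these. Larger figures, such as a 9-point false subgroup difference, need heavy permanent loss and ignore the active rounds in section 4.6. That loss differs by centre, stage or period is plausible but not stated.

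**Conclusion.** The point holds in a conditional form. Sections 3.4 and 4.6 together allow deaths to be found after contact ends but never extend follow-up for survivors by the same route. If later linked deaths count, censoring of the primary outcome depends on the outcome, and 5-year OS is probably biased, usually downward. With non-informative loss and complete linkage, the fall is about 1 point at 10% loss, 2 to 3 at 20% and 6 to 9 at 50%, and smaller where survivors are re-contacted. All loss and linkage rates are assumptions. The direction is not assured: with contact ending shortly before death and incomplete linkage, OS can be overstated. Distortion of subgroup and period comparisons is a possibility that depends on unequal loss. Section 3.4 needs to be changed whichever reading is meant.

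**What to change.** Amend section 3.4 so that one rule governs deaths and survivors:

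1. For patients submitted to NCDL linkage with no death found, censor at a stated date through which CDC death data are complete. Count no deaths after that date.
2. For patients who cannot be linked, censor at last contact.
3. As a sensitivity analysis, censor everyone at last contact and ignore later deaths known only from linkage. State that this is valid only if loss is non-informative.
4. Report linkage sensitivity against deaths confirmed by telephone or visit, by centre and year.

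The cost is one paragraph, one cut-off date, one extra OS run, and a tabulation from data the study already plans to collect. The amendment needs ethics approval under section 6.4.

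The downside is that the linkage-date rule overstates OS when linkage is incomplete: about 42.5% against a true 40% at 20% loss and 50% linkage. It should therefore be primary only where item 4 shows near-complete linkage. Neither rule is safe when loss is informative and linkage is poor, and the report should say so.
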